## Outcome measures and analysis

The primary outcomes are as follows: 1) safety via biomarkers of systemic inflammation (C-reactive protein), lipids (total cholesterol, high-density lipoprotein cholesterol, low-density lipoprotein cholesterol and triglycerides), sodium, liver enzymes (alanine aminotransferase, aspartate transaminase, alkaline phosphatase, albumin, bilirubin, total protein, nutritional ketosis (β-hydroxybutyrate) and glycemic status (fasting blood glucose and insulin)); 2) neurological recovery (AIS) motor and sensory scores and EPTs; 3) functional independence (SCIM); 4) microbiome composition; and 5) serum biomarkers (targeted proteomics).

In compliance with goals of the National Institute of Neurological Disorders and Stroke common data elements initiative, we are utilizing portions of the SCI common data elements that are expected to increase the efficiency and effectiveness of our clinical research study and diet intervention, increase data quality, and facilitate data sharing and comparisons across studies. For data analyses and results reporting, we adhere to the guidelines for reporting results using the international spinal cord core dataset [28].

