### Power calculations

Power calculations were performed using nQuery Advisor + nTerim 3.0, and assume a two-sided statistical test and a significance level of 5%. We obtained estimates of the standard deviation for the motor score of 23.5 and for the light touch score of 33 (both based on our preliminary data). With a final sample size of 24 participants per group, and also assuming a two-group *t* test and the prior assumptions, we have 80% power to detect between-group differences of 19.5 in the motor score and 27.3 in the light touch score as being statistically significant. With a final sample size of 24 participants per group, and assuming a paired *t* test and the prior assumptions, we have 80% power to detect within-group changes of 14.1 in the motor score and 19.8 in the light touch score as being statistically significant. All of these differences are approximately at the same levels as those that Kramer et al. detected as being statistically significant and clinically meaningful [36]. We believe that these estimates are conservative since we are performing our primary statistical analyses for between-group and within-group comparisons simultaneously using statistical methods that are more sophisticated than those that are assumed here. Given our history in SCI patient recruitment and the large SCI patient base at the UAB SRC, we fully expect to meet our recruitment goal.

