### Statistical analysis

Statistical analyses for neurological recovery will include comparisons of means of motor and sensory function, functional independence and serum measurements (e.g., glucose, insulin, alanine aminotransferase and aspartate transaminase) between the two groups, as well as comparisons within each group of the changes from baseline to rehabilitation to discharge (which should take approximately 5 weeks). Descriptive statistics, including measures of central tendency (sample mean, sample median) and dispersion (variance) will be calculated for each group. For safety outcomes, instead of comparing the two groups to the established standard safety values, we will compare circulating levels of proposed outcomes at the various time points among the two groups. If there are no significant group differences in these outcomes, we will conclude that the KD intervention is safe. We will also calculate 95% confidence intervals for the mean group differences for these outcomes as an additional check on safety and feasibility. The primary method of analysis will be analysis of covariance (ANCOVA), regressing the 5-week outcomes (safety, motor and sensory recovery, functional independence, and glycemic state) on the randomly assigned diet, baseline values of the measures, and other covariates such as age and sex. Repeated measures ANCOVA will also be used. Statistical assumptions will be assessed using box plots, residual plots and normal probability plots. Secondary analyses, accounting for all time points, will be conducted using mixed linear models, including repeated measures models. An appropriate structure for the covariance matrix (e.g., the unstructured covariance matrix) will be selected for these models using the final data. When a model term is statistically significant, the Tukey–Kramer multiple comparisons test will be used to determine which specific pair of means are significantly different. This method will allow us to compare changes over time (within-group changes) and differences between groups simultaneously. Covariates (e.g., length of enteral and solid feeding and length of stay in acute and rehabilitation care) will be accounted for in these analyses. Overall cross-sectional between-group comparisons, such as baseline comparisons used to examine pretest parameters, may be performed using the two-group *t* test, and overall within-group comparisons may be performed using the paired *t* test. If assumptions of normality of distribution for the above tests are not tenable, variables may be transformed prior to analysis, or appropriate nonparametric tests, such as the Wilcoxon rank-sum and signed-rank tests, may be used. Statistical tests will be two-sided and will be performed using a 5% significance level. Stratified analyses accounting for different injury levels will also be performed. These analyses will be specific to the distribution of data in each individual subgroup, which will minimize heterogeneity and allow us to analyze subgroups that may be more statistically homogenous and clinically relevant. SAS software, version 9.4 or later, will be used to conduct the statistical analyses. Multiple imputation methods will be used to address missing data for variables with moderate amounts of missing data (≥10%) and after examining whether data are missing completely at random, missing at random, or missing not at random. Missing data analysis will not be performed on variables with <10% missing data to avoid statistical bias larger than that obtained through the use of complete case analysis.

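### Five unranked primary domains have no error control across outcomes, and two sections disagree on which analysis is primary

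*Protocol article*

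**What the plan says.** Outcome measures and analysis opens with "The primary outcomes are as follows: 1) safety via biomarkers of systemic inflammation" and continues to neurological scores with EPTs, SCIM, microbiome composition and targeted proteomics. All five domains carry the label primary, and none is placed ahead of another.

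Statistical analysis sets the error rate: "Statistical tests will be two-sided and will be performed using a 5% significance level". Two adjustments are stated there. The between-group protein tests at discharge use an FDR of 0.2. Within a model that has a significant term, the Tukey–Kramer "multiple comparisons test will be used to determine which specific pair of means are significantly different".

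Power calculations uses a "standard deviation for the motor score of 23.5 and for the light touch score of 33", with 24 completers per group. Each variable gets its own 80% power at an undivided two-sided 5%, both for a between-group difference and for a within-group change.

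On the primary analysis, Power calculations says "we are performing our primary statistical analyses for between-group and within-group comparisons simultaneously". Statistical analysis says "The primary method of analysis will be analysis of covariance (ANCOVA), regressing the 5-week outcomes". It labels the mixed models secondary, and it is in that mixed-model text that the simultaneous comparison of changes over time and group differences is described.

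**The concern.** A 5% error rate describes a trial's conclusion only if the plan says which test carries that conclusion. Here several efficacy variables can each be reported as a primary result at 5%, and no rule says which, or how many, must succeed. The 80% power is likewise a statement about one variable tested alone.

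The disagreement over the primary analysis widens the choice. If simultaneous between- and within-group comparison is primary, a change inside the KD arm is part of the primary analysis. Such a change mixes any diet effect with natural recovery. The article recognises that recovery: its exclusion criteria remove suspected central cord syndrome because substantial spontaneous neurorecovery is expected there. Only the randomised between-arm contrast removes it.

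**Working it through.** **1. The plan's own figures.** Inputs from Power calculations: SD 23.5 (motor) and 33 (light touch), 24 per group, two-sided 5%.

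- Two-group t test, 46 df, noncentrality = difference / (SD × √(2/24)). Motor: 19.5 / (23.5 × 0.2887) = 2.87, power 80.3%. Light touch: 27.3 / (33 × 0.2887) = 2.87, power 80.1%.
- Paired t test, 23 df, noncentrality = change / (SD / √24). Motor: 14.1 / 4.80 = 2.94. Light touch: 19.8 / 6.74 = 2.94. Power is 80.4% for both.

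The stated 80% reproduces, one variable at a time with the whole 5%.

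**2. Chance of at least one false positive.** The article gives no count of efficacy variables, so the sets below are my reading. Five: motor, light touch, pin-prick, EPT (taken as one variable) and SCIM. Seven: these plus glucose and insulin, which are listed under safety but also named as benefits (glycemic control) in the Abstract and Background.

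For k independent tests with every null true, the chance is 1 − 0.95^k:

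- k = 2 (the two powered variables): 1 − 0.9025 = 9.75%
- k = 5: 22.6%
- k = 7: 30.2%

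The outcomes will be correlated, and the article gives no correlations. I assumed a common value r and simulated Z_i = √r·G + √(1−r)·E_i, counting draws with any |Z_i| > 1.96:

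| Correlation r (assumed) | 5 variables | 7 variables |
|---|---|---|
| 0 | 23% | 30% |
| 0.3 | 21% | 27% |
| 0.5 | 18% | 23% |
| 0.7 | 15% | 18% |

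**3. What sharing the 5% would cost.** Power for the 19.5-point motor difference at 24 per group, Bonferroni level 0.05/k:

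| k | Level | Power | Per group for 80% |
|---|---|---|---|
| 1 | 0.05 | 80% | 24 (as planned) |
| 2 | 0.025 | 71% | 29 |
| 5 | 0.01 | 58% | 36 |
| 7 | 0.0071 | 53% | 39 |

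The planned size supports 80% only where one endpoint carries the full 5%.

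**4. The two descriptions of the primary analysis.**

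| Section | Primary | Where the simultaneous comparison sits |
|---|---|---|
| Power calculations | Between- and within-group comparisons made together | In the primary analysis |
| Statistical analysis | ANCOVA of the 5-week outcomes on assigned diet, baseline and covariates | In the mixed models, labelled secondary |

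The first calls primary what the second calls secondary. The first also uses that description to argue that its power estimates are conservative.

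**The case against.** Much can be said for the plan. This is a journal article, and a fuller analysis plan may exist and set a hierarchy. Statistical analysis does name ANCOVA explicitly, while the phrase in Power calculations is an aside about conservatism, so one sentence could reconcile them. Both points bear on how easy the fix is. They do not remove the five unranked primary domains, the 5% rule or the conflict from the published text.

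Three stronger readings are tempting, and the article does not support them.

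- **That a chance primary success is more likely than not.** Counting every named variable gives 15 safety + 4 neurological + 1 SCIM + 8 microbiome + 4 protein = 32. The 28 outside proteomics give 76% if independent. But a significant difference in most safety laboratory values counts against the diet, since the article concludes safety when no group difference is significant. β-hydroxybutyrate is meant to differ by design. The discharge protein tests have their own FDR, so not every domain is tested at a plain 5%. The 76% also falls to 49% at correlation 0.5 and 33% at 0.7. It is not the rate of false efficacy claims.
- **That Tukey–Kramer robs the primary test of power.** It is attached to the secondary mixed models and acts only after a significant model term. The week-5 ANCOVA is a single two-group contrast and pays no such penalty.
- **That the trial will treat improvement in KD alone as proof of benefit.** No section says so. Within-group tests are planned and powered, so their role needs stating, but the misuse would be conjecture.

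**Conclusion.** The point holds. The article gives no single primary hypothesis and no control across outcomes, and its two statements of the primary analysis conflict. For efficacy, the chance of at least one false positive is about 15–23% over five variables and 18–30% over seven, against a nominal 5%. These figures assume that all nulls are true, that each variable is tested once at 5%, and that a common correlation lies between 0.7 and 0. They do not count within-group tests, repeated time points or EPT by dermatome. The 80% power is correct as computed, but it describes the trial's conclusion only if one powered between-group contrast is named as primary.

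**What to change.** Before the analysis is unblinded, amend the plan as follows.

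1. Name one primary hypothesis: the KD minus SD difference at week 5, by baseline-adjusted ANCOVA at two-sided 5%. The total motor score is the natural choice because the motor score is already powered. Power calculations says only motor score, so the amendment should state that the total is meant.
2. Test any further confirmatory outcomes in a fixed sequence that the sponsor sets, for example light touch and then SCIM, each only if the one before succeeds. This keeps the overall rate at 5% and leaves the stated 80% for motor intact.
3. Make the remaining outcomes secondary or exploratory, reported with confidence intervals.
4. Correct Power calculations to match Statistical analysis, and label within-group changes descriptive.

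No extra participants are needed. The costs are that fewer outcomes can carry a confirmatory claim, and that the change must be documented as an amendment made during the trial. Enrolment opened in September 2019 and participants know their allocation, so the amendment should record its date, its reason, and that the statistician and examiners were still blinded.

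### Separate within-level tests cannot show whether the diet effect differs by injury level; one model with a diet-by-level term, labelled exploratory, should replace them

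*Protocol article*

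**What the plan says.** The Statistical analysis section of the protocol article names ANCOVA of the 5-week outcomes on randomized diet, baseline value and covariates such as age and sex as the primary method. It allows transformation or nonparametric tests where normality is not tenable. It then states: "Statistical tests will be two-sided and will be performed using a 5% significance level". The next sentence reads: "Stratified analyses accounting for different injury levels will also be performed". The method is described in one clause: "These analyses will be specific to the distribution of data in each individual subgroup". The reason given for working this way is that it is an approach "which will minimize heterogeneity and allow us to analyze subgroups that may be more statistically homogenous and clinically relevant".

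The section does not give the number of levels, their boundaries or their expected sizes. Eligibility covers cervical and thoracic injuries from C5 to T12. Randomization is 1:1 in blocks of four, and no injury-level stratum is named.

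The Power calculations section concerns the whole sample only. Its basis is "With a final sample size of 24 participants per group". Its conclusion for the two-group comparison is that "we have 80% power to detect between-group differences of 19.5 in the motor score and 27.3 in the light touch score", and this rests on a "standard deviation for the motor score of 23.5 and for the light touch score of 33".

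**The concern.** The article states a way of studying injury level, and that way does not answer the question a reader will bring to it. A test of diet within cervical patients and another within thoracic patients each ask whether there is an effect at that level. Neither asks whether the effects differ. Each is also run on a fraction of a sample that was sized for one overall comparison, so a split result is likely even when the diet does exactly the same thing at both levels.

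Two features add to this. First, tying the analysis to each subgroup's own distribution can be read as allowing a different scale or test in each level, given that the same section permits transformation and rank tests. The level estimates would then not be directly comparable. Second, each level adds a further chance of a significant result on every outcome.

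At stake is the interpretation of a small trial. Chance could suggest that the diet works at one injury level and not at another, and the stated rationale would lend that impression some weight.

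**Working it through.** **Inputs from the protocol article.** 24 evaluable per arm; two-sided 5%; motor difference 19.5 with SD 23.5; light touch difference 27.3 with SD 33 (all Power calculations).

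**Assumptions, because the article gives no figures for subgroups.** Two levels of equal size, so 12 per arm in each; the same true effect in both; the full-sample SD within each level. Each is varied below.

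**Step 1: reproduce the plan's figure.** Two-group t test, noncentrality δ / (SD × √(2/n)).
- Motor, n = 24: standard error 23.5 × √(2/24) = 6.78; noncentrality 19.5 / 6.78 = 2.87; 46 degrees of freedom; power 80.3%.
- Light touch, n = 24: noncentrality 27.3 / 9.53 = 2.87; power 80.1%.

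Both agree with the stated 80%.

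**Step 2: power within one level.** Motor, n = 12 per arm: standard error 23.5 × √(2/12) = 9.59; noncentrality 19.5 / 9.59 = 2.03; 22 degrees of freedom, critical value 2.07; power p = 49.4%.

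**Step 3: split significance under an identical effect.** The levels contain different patients, so the two tests are independent.
- Exactly one significant: 2p(1 − p) = 2 × 0.494 × 0.506 = 50.0%.
- Both: p² = 24.4%. Neither: (1 − p)² = 25.7%.

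Simulation of 100,000 trials gives 50.2% for exactly one.

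**Step 4: the interaction test on the same data.** Its null hypothesis is true here, so it should reject 5% of the time. Simulation gives 5.1%, for a 12/12 split and for a 16/8 split.

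**Step 5: sensitivity of the 50%.**

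| Varied input | Exactly one level significant |
|---|---|
| Split 14/10 per arm | 51% |
| Split 16/8 | 54% |
| Split 18/6 | 59% |
| SD 20 (12/12) | 47% |
| SD 17 | 36% |
| SD 15 | 24% |
| SD 12 | 6% |
| True effect 0.5 × 19.5 | 27% |
| True effect 1.5 × 19.5 | 28% |
| True effect 2 × 19.5 | 5% |

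With three levels of 8 per arm, power is 34.0% in each, and the three tests disagree 67% of the time. The split between levels matters little. The residual SD and the true effect matter a great deal.

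**Step 6: no true effect.** At least one of two level tests is significant with probability 1 − 0.95² = 9.75%. Adding the overall test, which is correlated with both, gives 11.7% by simulation (200,000 trials): about 12% for one outcome, against 5% for the overall test alone.

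**Step 7: power of the interaction test.** The standard error of the difference between two level effects with 12 per cell is 23.5 × √(4/12) = 13.57. For a 19.5-point difference between levels the noncentrality is 19.5 / 13.57 = 1.44; 44 degrees of freedom; power 29%.

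**The case against.** A condensed article may leave an interaction term, subgroup definitions, an exploratory label and multiplicity rules to a full protocol or SAP. That stands: their absence alone would not be a finding. The point survives because the article goes further and states the method, within-subgroup analysis, with a reason for it. An SAP that followed the text would carry the method forward. The article does name a time-by-treatment term for the microbiome and a false discovery rate for proteomics, so such detail is not beyond its scope.

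The 50% needs two levels, the design effect and the unadjusted SD inside each level. The article fixes none of these, and the planned baseline adjustment should lower the residual SD. This also stands, and the figure must be quoted with its conditions.

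Four stronger readings are tempting, and the document does not support them:
- A reader might infer that a split result would be reported as a level-specific effect. No such rule is stated. The 50% is the chance of discordant p-values, not of a false report.
- A reader might infer that the subgroups are put on a par with the overall contrast. They are not: ANCOVA on randomized diet is named as primary, the power calculation covers the whole sample only, and the stratified analyses come as an addition.
- A reader might infer that the subgroup results are presented as more clinically relevant than the overall result. The wording is hedged and makes no explicit comparison with the overall result.
- A reader might infer that different tests will be chosen in different levels. The sentence on subgroup distributions is vague and may mean only that analysis is done within each level. That is a reason to remove it, not evidence of a plan to mix methods.

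That each level is tested at 5% is itself an inference from the general sentence on significance, although a fair one.

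**Conclusion.** The point holds in a limited form. The stated within-level analyses cannot establish whether the diet effect differs by injury level, and the plan's own design figures show how easily they could mislead. With two equal levels, a true motor effect of 19.5 in both and SD 23.5, exactly one level is significant about 50% of the time, against about 5% for an interaction test. Across the assumptions tried, disagreement runs from about 5% to 67%; a tighter residual SD after baseline adjustment would bring it down. Under no effect, the chance of at least one significant result per outcome is about 12% with the overall test and two level tests.

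The primary ANCOVA is not affected. The change is worth making before analysis because it concerns what may be concluded about injury level, and it is cheap.

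**What to change.** Keep the overall ANCOVA as primary. Replace the level-by-level tests with an injury-level main effect and a diet-by-injury-level interaction in that same model, using a grouping fixed in advance (for example cervical/thoracic). Report the interaction estimate and the diet effect in each level with 95% confidence intervals, all from that one model and on one common scale. Label these results exploratory, and state that no efficacy claim will rest on a single level's p-value. Delete the sentence that makes the analyses specific to each subgroup's data distribution.

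The cost is some wording and two additional model terms. Neurological level is already assessed for eligibility, so no new data are needed. Significance within a single level can no longer be claimed. The interaction test will also be weak, with about 29% power for a 19.5-point difference between levels at 12 per cell and SD 23.5. The text should therefore say that a non-significant interaction is not evidence of equal effects, and that the confidence interval carries the information.

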
For microbiome analysis, alpha diversity indices will be analyzed using linear mixed-model with time (pre- and post-) and group (KD and SD) as fixed factors and participant as a random effect. Permutational multivariate analysis of variance testing will be used to assess the effects of time, treatment, and time × treatment on beta diversity indices. The principal coordinate analysis will be performed to visualize the beta diversity distance matrices [18].

For targeted proteomics, three specific analytic approaches will be utilized. First, two-sample *t* tests, or Wilcoxon rank-sum tests if the normality assumption is questionable, will be used to examine differences in the number of selected peptides and proteins between diet groups at discharge (approximately 5 weeks). Because of the number of proteins to be examined, a false discovery rate of 0.2 will be used to account for multiple hypothesis tests. The second approach will examine the manner in which levels of selected peptides vary across the longitudinal time points of baseline, rehabilitation and discharge. To examine these patterns, mixed linear models such as repeated measures models using time as a within-person factor and diet as a between-person factor will be constructed. Finally, Pearson’s correlation will be used to measure the strength and direction of linear associations between selected peptide levels and 5-week outcomes of safety, neurological, functional and glycemic status. 

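### The alpha-diversity model as written has no group-by-time term and no baseline adjustment, so its group coefficient estimates half the diet effect; the discharge-only protein test is unbiased but could be more efficient

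*Protocol article*

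**What the plan says.** All of this is in the protocol article, mainly under Statistical analysis.

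- **Alpha diversity:** "alpha diversity indices will be analyzed using linear mixed-model with time (pre- and post-) and group (KD and SD) as fixed factors". A random participant effect completes the model. No interaction and no baseline covariate are named.
- **Beta diversity, next sentence:** a permutational test "will be used to assess the effects of time, treatment, and time × treatment on beta diversity indices".
- **Proteins, first approach:** two-sample t or Wilcoxon tests "will be used to examine differences in the number of selected peptides and proteins between diet groups at discharge". For these, "a false discovery rate of 0.2 will be used to account for multiple hypothesis tests".
- **Proteins, second approach:** this looks at how "levels of selected peptides vary across the longitudinal time points of baseline, rehabilitation and discharge", and "repeated measures models using time as a within-person factor and diet as a between-person factor will be constructed".
- **Proteins, third approach:** Pearson correlations of peptide levels with the 5-week outcomes.

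Under Outcome measures and analysis, microbiome composition and serum biomarkers are both among the primary outcomes. The baseline-adjusted ANCOVA named as the primary method lists safety, neurological recovery, function and glycaemia as its outcomes. It lists neither microbiome nor proteomics.

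**The concern.** In a two-arm trial with one measurement before the diet and one at its end, the diet effect is the difference between arms at the second measurement, with or without adjustment for the first. A model with additive time and group terms forces the arms to differ by the same amount at both times. Before the diet they should not differ at all, so the model spreads the post-diet difference over two time points, one of which cannot carry it.

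The time coefficient does not help: it averages the change in the two arms. An analyst who follows the text would report too small a diet effect on all five alpha-diversity indices and would often miss a real one.

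For proteins the matter is milder. Baseline serum is collected, and the first approach, which carries the multiplicity control, makes no use of it. That approach also speaks of the number of peptides and proteins, while the other two speak of levels. The targets are chosen in advance and quantified, so a count is not the quantity of interest.

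**Working it through.** **Inputs from the article.** Allocation is 1:1 (Study design and participants). Power calculations gives a final 24 per group, a two-sided 5% level, motor-score SD 23.5 and detectable difference 19.5.

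**Inputs assumed.** The article gives no SD, effect size or pre-post correlation for alpha diversity or proteins. I borrow the motor-score effect, D = 19.5/23.5 = 0.83 SD, and show correlations ρ of 0.3, 0.5 and 0.7. The SD is taken as 1 at both times, and every participant has both measurements.

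**The plan's own figure.** Two-group t test, n = 24 per arm: noncentrality 0.830/√(2/24) = 0.830/0.289 = 2.87 on 46 df, power 80.3%. This agrees with the stated 80%.

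**Expectation and variance of each estimator (n per arm):**

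- Main effects only: the group coefficient is the difference between arms in participant means. Expectation (0 + D)/2 = D/2; variance (1+ρ)/n.
- Group-by-time coefficient: expectation D; variance 4(1−ρ)/n.
- Discharge-only comparison: expectation D; variance 2/n.
- ANCOVA on baseline: expectation D; variance 2(1−ρ²)/n.

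**Worked case, ρ = 0.5.**

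- Main effects: (0.830/2)/√(1.5/24) = 0.415/0.25 = 1.66, power 37%.
- Group-by-time: 0.830/√(2/24) = 2.87, power 80%.
- ANCOVA: 0.830/√(1.5/24) = 0.830/0.25 = 3.32, power 90%.

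At this correlation the main-effects and ANCOVA standard errors are equal, so the whole loss comes from the halved estimate.

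| Analysis | Share of D estimated | ρ = 0.3 | ρ = 0.5 | ρ = 0.7 |
|---|---|---|---|---|
| Main effects only | 0.50 | 42% | 37% | 33% |
| Group-by-time coefficient | 1.00 | 66% | 80% | 95% |
| Discharge only | 1.00 | 80% | 80% | 80% |
| ANCOVA | 1.00 | 84% | 90% | 98% |

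**Check.** In 20,000 simulated trials at each correlation, the main-effects estimate was 0.50 of D and the other three were 1.00 of D. Simulated power was within about one percentage point of the table. In 150 trials at ρ = 0.5 analysed with a fitted main-effects mixed model, the mean group coefficient was 0.50 of D.

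**Proteins.** The last two rows of the table apply. The discharge test recovers all of D. ANCOVA multiplies its variance by 1−ρ², which is 0.91, 0.75 and 0.51 at the three correlations. At ρ = 0.3 that moves power only from 80% to 84%. These figures use a per-test 5% level, whereas the plan controls a false discovery rate of 0.2, so they show relative efficiency only.

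**The case against.** The best defence is that naming time and group as fixed factors is common shorthand for a factorial model that includes their interaction, that the article is condensed, and that a full analysis plan may say so. This is possible, and it limits how firmly the point can be put. But the article is not silent: it lists the terms, and the adjacent sentence spells out the interaction for beta diversity. The literal reading is the more natural one, and under either reading the text should state the term.

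A reader might also infer more than the documents support:

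- *That the protein comparison is biased.* It is not. Under randomisation a discharge-only comparison estimates the full diet effect; only precision is lost, and little of it at low correlation.
- *That all protein analyses ignore baseline.* The second approach includes baseline as a time point. It names no diet-by-time term either, but its model is described loosely and I make no point of it.
- *That the whole microbiome outcome is affected.* Beta diversity has its interaction.
- *That the peptide correlations must be adjusted for arm.* The Discussion suggests that the diet may act in part by lowering fibrinogen, so a diet-driven association is part of what is sought. The article does not say whether the arms are pooled, and it attaches no causal claim to the correlations.

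The reference to the number of peptides is probably loose wording, since levels are clearly meant elsewhere. It is an editorial correction.

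**Conclusion.** The point holds for alpha diversity as the model is written. Its group coefficient estimates half the post-diet effect, and no term estimates the effect itself. The halving needs only randomisation and paired samples; it does not depend on the correlation or the effect size. The power figures (42/37/33% against 84/90/98%) are illustrative, because 0.83 SD is borrowed from the motor score and the correlations are assumed. If the full plan already fits the interaction, what remains is a clarification of the article.

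For proteins the finding is one of efficiency in the first approach only, together with one word to correct.

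**What to change.** 1. **Alpha diversity (preferred):** for each index, analyse the post-diet value by ANCOVA with diet group as factor and the baseline value as covariate.
2. **Alpha diversity (alternative):** keep the mixed model, add group-by-time, and state that the test of the diet effect is the group difference at the post-diet time. This removes the bias. With separate baseline means for the two arms, however, that contrast is no more precise than a discharge-only comparison (80% in the table), and the interaction coefficient itself has 66% power at ρ = 0.3. ANCOVA is at least as powerful as either at every correlation.
3. **Proteins, first approach:** replace the two-sample test by ANCOVA of the discharge level on diet and baseline level, keep the false discovery rate of 0.2, and write levels in place of number.

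No new samples, visits or participants are needed, since blood and stool are already collected at baseline and repeated after 5 weeks. The cost is analysis wording, plus the written amendment and approvals that the Protocol amendments section requires for any change to the protocol. The change should be fixed before outcome data are compared by arm.
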